# Effect of Baduanjin exercise intervention on cognitive function and quality of life in women with breast cancer receiving chemotherapy: study protocol of a randomized controlled trial

**DOI:** 10.1186/s13063-021-05355-w

**Published:** 2021-06-19

**Keywords:** Baduanjin exercise, Breast cancer, Cognitive function, Quality of life

## Abstract

**Background:**

More than 50% cognitive impairment was reported by cancer patients before and after medical treatment. However, there are no effective interventions to manage the cognitive problem in women with breast cancer. This pilot study was designed to evaluate the protective effect of Baduanjin exercise on cognitive function and cancer-related symptoms in women with early-stage breast cancer undergoing chemotherapy.

**Method:**

A single-blinded, randomized control trial was designed. The trial will recruit 70 patients with early-stage breast cancer scheduled to receive chemotherapy from Shanghai in China. All participants will be randomly assigned to (1:1) the supervised Baduanjin group (5 times/week, 30 min each time) or the wait-list control group for 3 months. The effect of Baduanjin exercise intervention will be evaluated by outcome measures including subjective and objective cognitive function, symptoms (fatigue, depression, and anxiety), and health-related quality of life at pre-intervention (T0), 8 weeks (T1), and 12 weeks (T2). The PCI score in the FACT-Cog as the primary cognitive outcome will be reported descriptively, while effect sizes and 95% confidence intervals (CIs) will be calculated. The collected data will be analyzed by using an intention-to-treat principle and linear mixed-effects modeling.

**Discussion:**

This is the first randomized clinical trial to investigate whether Baduanjin exercise will have a positive role in improving cognitive function in women with breast cancer receiving chemotherapy. If possible, Baduanjin exercise will be a potential non-pharmacological intervention to manage cognitive dysfunction and promote survivorship care among breast cancer survivors.

**Trial registration:**

Chinese Clinical Trial Registry (ChiCTR) ChiCTR2000033152. Registered on 22 May 2020

**Supplementary Information:**

The online version contains supplementary material available at 10.1186/s13063-021-05355-w.

## Background

Cognitive dysfunction is a frequently reported side effect that cancer patients experience resulting from cancer and medical treatment (e.g., surgical resection, chemotherapy, local radiation therapy, and endocrine therapy), showing a cognitive decline in the field of memory, processing speed, attention, and executive functions [1–4], and it is also known as cancer-related cognitive impairment (CRCI). More than 50% of breast cancer patients have subjective cognitive complaints, and 15–25% of cancer patients have objective cognitive dysfunction [5, 6]. Cognitive impairment may persist for years beyond the completion of treatment for some patients [7]. Although the cognitive change is generally mild to moderate, it has a negative impact on the physiological condition, activities of daily living, professional achievement [8], treatment adherence [9], and overall quality of life of cancer survivors in the context of long-term cancer care [10, 11].

Currently, the biological mechanisms of CRCI are not identified, but there are several results based on animal and clinical studies. The mechanisms include (1) increase in the levels of chemotherapy-induced pro-inflammatory cytokines (e.g., IL-6, TNF-α) [12, 13]; (2) effects of chemotherapy-induced neurotoxicity on the brain structure and function (e.g., white matter damage [14], inhibition of neurogenesis [15], and changes in neurotransmitter [16]); (3) changes in the blood vessels and blood flow in the central nervous system [17]; and (4) direct and oxidative DNA damage [18]. In addition, pervasive fatigue and negative emotions may contribute to increased susceptibility of cognitive impairment [19]. It is unclear whether the cognitive impairment results from one mechanism or a combination of multiple effects.

However, there are currently no effective interventions to adequately alleviate or reduce the risk of cognitive impairment. Various forms of physical activity have been studied to improve cognitive function in healthy older adults and people with mild cognitive impairment (MCI) [20, 21]. Emerging preliminary results have demonstrated that physical activities are a potential intervention to improve cognitive function, but conflicting results have been reported. Two pilot studies [22, 23] showed that aerobic exercise improved objective cognition in patients with breast cancer after primary treatment. Hartman et al. [22] found that a 12-week exercise intervention improved the processing speed in patients diagnosed with breast cancer in the preceding 2 years, but there was no significant improvement in self-reported cognitive function. Another study showed that a 24-week supervised and home-based aerobic exercise program demonstrated similar results in postmenopausal women with early-stage breast cancer [23]. Nevertheless, Galvão et al. [24] showed that aerobic exercise plus resistance training improved subjective cognitive function from a subscale of health-related quality of life scale (EORTC-QLQ-C30) and decreased the level of C-reactive protein (CRP). The conflicting results of previous studies are likely due to the insufficient sample sizes and heterogeneity of types and timing of exercise interventions. Moreover, most of the studies used subjective cognitive scales instead of multidimensional measures of objective cognitive function. More rigorous and replicable clinical trials are warranted to prove potential benefits of physical exercise in breast cancer patients with cognitive problems.

In addition to aerobic exercise, research based on mind-body therapy have also achieved preliminary results in improving cognitive function among cancer patients [25–27]. In breast cancer survivors, mindfulness-based exercise may be superior to gentle exercise or survivorship support in terms of improving self-reported cognitive function and distress [25]. Oh et al. [26] demonstrated that a 10-week medical Qigong program significantly improved subjective cognition with medium effect size. Baduanjin, a traditional Chinese fitness exercise combining meditation and repetitive movement with low intensity [28, 29], is considered to be an effective exercise in promoting health [28]. Recently, a review [30] supported that Baduanjin exercise may be effective as an adjunctive rehabilitation method for improving cognitive function, but the effect of Baduanjin exercise on CRCI needs to be further explored.

Therefore, the primary purpose of this article is to describe the protocol of a randomized control trial to examine whether Baduanjin exercise program is a protective measure in improving cognitive function in chemotherapy-exposed patients with early-stage breast cancer.

The main aims of the trial are as follows:
Whether a 3-month Baduanjin intervention improves subjective and objective cognitive function of breast cancer patients during chemotherapyWhether a 3-month exercise intervention improves quality of life and cancer-related symptoms such as fatigue, depression, and anxietyWhether there is an association between subjective or objective cognitive function, symptoms, and quality of life

## Methods/design

### Study design

This is a single-blinded randomized control trial (RCT) with two study arms, including a supervised Baduanjin intervention group and a wait-list control group. An overview of the study is displayed in Fig. 1. The overall development of the study protocol followed the Standard Protocol Items: Recommendations for Interventional Trials (SPIRIT) guidelines [31]. The protection of human subject was approved by the Ethics Committee of the Seventh People’s Hospital of Shanghai University of Traditional Chinese Medicine.

**Fig. 1 Fig1:**
[figure not shown]
Overview of the study

### Study setting

Participants are recruited from the three affiliated hospitals of Shanghai University of Traditional Chinese Medicine, including Seventh People’s Hospital, Longhua Hospital, and Yueyang Hospital of Integrated Traditional Chinese and Western Medicine. The outcome measures are evaluated in a quiet room in the hospital to avoid interference.

### Recruitment

Recruitment of breast cancer patients started in 1 June 2020. Researchers can screen breast cancer patients who meet the inclusion and exclusion criteria through electronic medical records, and provide information brochure of the study, as well as possible benefits of the exercise and the relevant safety during the trial, in order to obtain informed consent. In addition, recruitment posters will be posted in the hospitals and via social media such as WeChat, an online communication app. After consent is obtained, the research team will screen the candidates with patients’ questionnaire and neuropsychological testing. Other parameters, including height and weight to calculate body mass index (BMI), will also be recorded.

### Inclusion criteria

The inclusion criteria meeting this study are as follows:
Female patients newly diagnosed with stage I to III breast cancerScheduled to receive adjuvant chemotherapyAged 40 to 75 yearsUsing WeChatSufficient fluency of the Chinese languageWilling to participate in the study and be randomly assigned

### Exclusion criteria

The patient will be excluded for meeting any of the following criteria:
Disease recurrence or metastasisKnown conditions and/or diseases that impact cognition (e.g., Alzheimer’s disease, dementia, or other psychological diagnoses)Disorders that might preclude exercise participation (e.g., fracture, arthritis)Current/planned participation in mindfulness-based exercise programs (e.g., TaiChi or Qigong)

### Randomization and blinding

Participants will be randomly assigned to 1 of 2 groups—an intervention group or a control group—in a 1:1 ratio using the SPSS 24.0 software. The allocation of the result will be put into sealed, opaque envelopes by a study administrator not involved in the study, and the group numbers will be subsequently disclosed. Given that Baduanjin exercise is a well-known exercise to the study population, blind method is conducted to assessors only, not physicians or patients. In addition, all participants will be asked not to discuss the practice with each other to minimize bias. The assessor will also be instructed not to acquire the participant’s exercise information. Participants are allowed to withdraw without giving a reason at any time. If any patient experiences adverse effect during exercise, such as palpitation or severe upper limb lymphedema, but still wishes to participate, there will be a therapist available who will evaluate whether the patient can continue on the study.

### Interventions

Upon completion of baseline testing and randomization, participants are notified of the group assignment by the unblinded project director. At that time, a participant’s group assignment and baseline assessment will be conducted within 3 days of beginning chemotherapy.

### Baduanjin exercise group

Baduanjin exercise is conducted according to the standards promulgated by the General Administration of Sport in China in 2003, which consists of 10 postures (including the beginning and ending posture). A professionally trained Qigong specialist will uniformly train subject researchers to learn Baduanjin. Researchers will then conduct on-site instruction to guide patients and correct their movements. Participants will also be provided with video demonstration. Before the first cycle of chemotherapy, the patients will conduct the first session in the hospital, then follow the video workout at home. Recommended training time is 5 times a week, for half an hour each time, during the 12-week study period. The program begins with stretching the joints, inhalation and exhalation for 2 min respectively, and two 12-min Baduanjin sessions, followed by 2 min of muscle relaxation exercises. Patients’ log will be recorded including any obstacles during exercise at home. When the patients go to the hospital to receive chemotherapy, the feedback of exercise log will be collected and checked. To promote participant retention, we will follow up and encourage the patients through WeChat twice weekly, asking the factors that hinder their activities and solving it in time. In addition, small gifts will be given to patients (e.g., towels and toothbrushes) to promote their exercise enthusiasm at each assessment.

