### Wait-list control group

Patients randomized to the control group are given a face-to-face health education according to the handbook to maintain their usual healthy lifestyle. Disease-related questions raised by the patients will be directly communicated or answered through WeChat online. Meanwhile, researchers need to ask patients about their conditions twice a week. Patients can exercise the affected limb through exercises including abduction, forward flexion, backward extension, internal rotation, and wall climbing, according to the guideline and standard for the diagnosis and treatment of breast cancer set forth by the Chinese Anti-Cancer Association (2019 edition), and the patients are not asked to conduct other aerobic activities. The supervised Baduanjin exercise for participants will be offered if they wish after the completion of study.

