### Study assessments

Cognitive ability and several patient-reported outcome (PRO) questionnaires will be collected as primary outcome and secondary outcomes, respectively. These outcome assessments will be carried out by professional researchers at pre-intervention (T0), 8 weeks (T1), and 12 weeks (T2) during intervention. The most important primary outcome is cognitive ability, which is assessed using Cancer Therapy-Cognitive Function (FACT-Cog). If there is a 7-point improvement in the FACT-Cog PCI score between the groups, then the intervention will be thought to have tended to have a beneficial effect based on minimal clinically important difference (MCID) [32]. Demographic information collected via interview pre-intervention include patients’ age, level of education, and economic status. Disease information is retrieved from medical records by two trained study coordinators ([name], [name]). The schedule of study outcome assessments is outlined in Fig. 2.

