### Cognitive ability

Patients’ subjective feelings are the most relevant measures of clinical significance, and cognitive complaint reported by patients is the main outcome indicator. The Functional Assessment of Cancer Therapy-Cognitive Function (FACT-Cog) was developed by Wagner et al. [33] to assess subjective cognitive function, and revised Chinese version will be used in this study [34]. The scale was divided into 4 dimensions including 37 items: perceived cognitive impairment (PCI), perceived cognitive ability (PCA), evaluation of others, and impact on quality of life (QoL). The higher the score of the overall cognitive impairment, the better the cognitive function. Cronbach’s α coefficient is from 0.87 to 0.96 with good internal consistency.

In addition, the International Cognition and Cancer Task Force (ICCTF) [1] proposed and considered the objective neuropsychological test battery to be the gold standard for evaluating cognitive function of CRCI. The Hopkins Verbal Learning Test-Revised (HVLT-R) [35] is a test used to assess verbal learning and memory. The Chinese version of HVLT consists of a 12-word list, and the researcher will read them aloud. The patient needs to recall as many words as possible for three consecutive learning trials (total recall). After 20 min, the patient will be asked again to recall (delayed recall). Lastly, a list of 24 words will be read by the researcher, and the patient will be required to declare and answer whether the particular word is mentioned in previous list (recognition). At the subsequent follow-up, a parallel version of HVLT (the 12-word list with different words) is applied to replace the original version. In addition, executive function and attention are evaluated by the Trail-Making Test (TMT) [36] and Digit Symbol Substitution Test (DSST) [37], respectively (see Table 1).

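### Gifts at each assessment are described for the exercise arm alone, which ties an apparently arm-specific reward to the visits where unblinded patients self-report the primary outcome

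*Protocol article*

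**What the plan says.** The gift is described in one place, the Baduanjin exercise group section of the Protocol article: "small gifts will be given to patients (e.g., towels and toothbrushes) to promote their exercise enthusiasm at each assessment". The sentence before it gives a different measure and purpose: "To promote participant retention, we will follow up and encourage the patients through WeChat twice weekly". The same section has exercise logs collected and checked when patients attend for chemotherapy.

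The Wait-list control group section lists health education, answers over WeChat, matched contact ("researchers need to ask patients about their conditions twice a week"), permitted limb exercises and an offer of Baduanjin after the study. It names no gift. It also says that "the patients are not asked to conduct other aerobic activities".

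Under Randomization and blinding, "blind method is conducted to assessors only, not physicians or patients". The stated safeguard is: "The assessor will also be instructed not to acquire the participant’s exercise information". Under Cognitive ability, "cognitive complaint reported by patients is the main outcome indicator". Study assessments sets the visits at "pre-intervention (T0), 8 weeks (T1), and 12 weeks (T2) during intervention".

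**The concern.** A reward given in one arm at the moment of outcome measurement can act in three ways.

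- **Reporting.** FACT-Cog PCI, fatigue, mood and quality of life are all reported by patients who know their arm. A reward for exercise enthusiasm at that visit may encourage favourable answers, and blinding the assessor does not protect against this.
- **Attendance.** A gift for coming to the assessment may keep more patients in one arm than in the other, so that outcome data go missing at different rates.
- **Assessor blinding.** The assessor is the only blinded party. A towel or toothbrush that only one arm receives is a visible cue, and the stated safeguard covers exercise information, not gifts. This bears on the assessor-administered tests; the self-reported primary outcome is already open to the patient's knowledge of allocation.

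At stake is whether a modest difference between arms could be put down to Baduanjin alone.

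**Working it through.** The plan gives no figure on this point, so there is none to reproduce. The check is first a comparison of sections, then an illustration.

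**Is the gift arm-specific?**

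1. It appears under the exercise-arm heading only.
2. Its stated purpose is exercise enthusiasm, which does not fit an arm given no exercise programme.
3. The control section describes that arm's contact and education and is silent on gifts.
4. Recruitment, Study assessments and Data collection do not extend it to both arms.

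The natural reading is that the gift belongs to the exercise arm. That is an inference from placement, purpose and silence; no sentence states it.

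**Is it tied to outcome measurement?** Yes, in so many words. The text does not say who hands it over, whether this is before or after testing, or whether the assessor is present.

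**How large could the effect be?** From the document: about 70 patients randomised 1:1, so 35 per arm; 58 evaluable at power 0.80; 20% dropout overall, not split by arm; two-sided 0.05. Everything else below is assumed.

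*Power.* The effect size behind 58 is not given; a two-sample t-test with 29 per arm implies d of about 0.75. With 35 per arm, dropout of 20/20, 15/25 and 10/30% (exercise/control) gives power of 78.6, 78.4 and 77.9%. The loss is trivial.

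*Informative dropout.* If dropouts score m SD worse than completers, the completer mean exceeds the full-arm mean by (dropout rate) × m. The bias in exercise minus control is m × (p_ex − p_con):

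- 15/25%: m = 0.5 gives −0.05 SD; m = 1.0 gives −0.10 SD.
- 10/30%: m = 0.5 gives −0.10 SD; m = 1.0 gives −0.20 SD.

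A second model, with dropout correlated r = 0.3 with worse PCI, has shift r × φ(z_p)/(1 − p). At p = 0.10 it is 0.3 × 0.1755/0.9 = 0.059; at p = 0.30 it is 0.3 × 0.3477/0.7 = 0.149; the difference is 0.09 SD. Higher PCI is better, so losing more poorly functioning controls works **against** Baduanjin.

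*Favourable reporting.* With 70 × 0.8 = 56 completers, 28 per arm, and no true effect, a reporting shift of 0.1, 0.2 or 0.3 SD in the exercise arm raises the two-sided 5% error to about 6.6, 11.4 or 19.7%. This works **for** Baduanjin.

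The two mechanisms oppose each other, and no input for either is in the document. Nor does the article give an SD for PCI, so these SD units cannot be set against its 7-point margin.

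**The case against.** The other side has substance.

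- **The gift may not be exclusive.** This is a journal article, and a towel for controls is a detail that a condensed text could omit. The baseline visit counts as an assessment, yet the Interventions section has allocation disclosed only after baseline testing and randomisation. A gift handed over during baseline testing could therefore not depend on arm. This stands: a reader might infer that controls certainly receive nothing, and the text does not say so.
- **The gift is not called a retention measure.** Its stated purpose is exercise enthusiasm; retention is the purpose of the preceding WeChat sentence. This stands. An adherence incentive can be a legitimate part of an exercise package. It does not explain why the incentive is given at outcome visits.
- **Controls have an incentive too.** They are offered Baduanjin after the study, and contact is twice weekly in both arms. This stands, so a wholly one-sided pull to stay cannot be claimed.
- **Unblinding is not shown.** A reader might infer that the assessor will learn the allocation. Nothing says the assessor gives or sees the gift, and an unblinded project director exists who could do it.
- **The gift does not depend on any score.** Patients' knowledge of their arm is the main source of reporting bias, and the article discloses it. Any added effect of a toothbrush is probably marginal.
- **The illustrations rest on assumed inputs.** A 10/30% dropout split caused by small gifts is extreme. The planned mixed model uses earlier visits from patients who drop out and may reduce the completer shift.

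What remains is the plain text: a reward described for one arm and timed to outcome measurement, where another occasion was already in the plan.

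**Conclusion.** The point holds as a minor one. As written, the plan attaches an apparently arm-specific reward to the visits where unblinded patients report the primary outcome, and this could cue the assessor of the objective tests if the gift is seen. It rests on reading the section placement, the stated purpose and the silence of the control section together.

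The effect is probably small. The assumed scenarios give 0.05 to 0.20 SD against Baduanjin from dropout, and an opposite effect from favourable reporting; these show the mechanism and are not estimates. The documents do not support a stronger reading, in which the trial is shown to be biased in a known direction or its assessor blinding is shown to be broken.

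**What to change.** Three changes of wording are enough:

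1. Give the same small item to both arms after each assessment (T0, T1, T2), described as thanks for attending, and handed over by unblinded staff out of the assessor's sight.
2. If an exercise incentive is wanted, tie it to the exercise-log collection at chemotherapy visits.
3. If controls already receive the item, say so; the point is then closed apart from how the item is handed over.

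The article expected completion by 1 June 2021, so some or all assessments may already have taken place. For those, the report should state who received gifts and how, and show dropout by arm and visit.

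The cost is items for about 35 control patients per visit, at most 35 × 3 = 105 in all, and a sentence or two of text. Sample size, outcomes and analysis do not change.
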